[figure not shown]

## ABSTRACT

The Substance Abuse and Mental Health Administration awarded State Targeted Response grants to support states' efforts to address the opioid epidemic. In Nevada, one component of this grant was mobile recovery outreach teams (MROT) that utilized peer recovery support specialists to provide care for qualifying patients in emergency departments (EDs). The Mobile Emergency Recovery Intervention Trial (MERIT) is a mixed methods study to assess the feasibility/acceptability and effectiveness of the MROT intervention. Data will be derived from state-level data sets containing de-identified emergency department visits, substance use disorder treatment records, and mortality files; in-person mixed methods interviews; participant observation; and self-report process evaluation forms. Primary outcomes include Medication Assisted Treatment (MAT) initiation and non-fatal overdose; secondary outcomes include MAT retention and fatal overdose. Quantitative hypotheses will be tested using generalized linear mixed effects models, Bayesian hierarchical models, and marginal Cox models. Qualitative interview data will be analyzed using an inductive thematic analysis procedure.

DOI

[dx.doi.org/10.17504/protocols.io.br95m986](https://dx.doi.org/10.17504/protocols.io.br95m986)

**protocols.io**  
<https://protocols.io/view/strategic-targeted-response-for-opioid-overdose-ev-br95m986>

[figure not shown]

## LICENSE

\_\_\_\_\_ This is an open access protocol distributed under the terms of the [Creative Commons Attribution License](#), which permits unrestricted use, distribution, and reproduction in any medium, provided the original author and source are credited

## CREATED

Feb 09, 2021

## LAST MODIFIED

Feb 09, 2021

## PROTOCOL INTEGER ID

47133

## Description

The over-arching goal of this research is to test the effectiveness of a Mobile Recovery

- 1 Outreach Team (MROT) intervention for opioid overdose and/or opioid use disorder patients treated in Nevada's Emergency Departments (EDs). MROT's will provide peer coaching and mentorship, referrals to medication-assisted treatment (MAT), and opioid overdose education and naloxone as part of the State's SAMHSA STR Program. We will accomplish the research goal through the following two aims: (1) Determine the effectiveness of the MROT on (a) subsequent overdose, and (b) MAT uptake among patients presenting to a hospital ED for opioid overdose, and (2) Evaluate the MROT implementation and fidelity through comprehensive process evaluation. In addition, the research will examine the feasibility and acceptability of a mobile team intervention model in rural Nevada. Because we know Nevada has a unique landscape with many cities located in rural/frontier areas where a traditional model may not be feasible, we will expand our feasibility/acceptability research and outcomes evaluation to include examining the impact of alternative models in hospitals in the rural/frontier regions of Nevada.

## Hypotheses

- 2 We hypothesize that in the 9 months following their index overdose, patients exposed to the MROT will: H1: be more likely than control participants to initiate MAT H2: be retained in MAT longer than control participants H3: have fewer non-fatal ODs than control participants H4: be less likely to die of a subsequent OD than control participants All analyses will be conducted using the intent-to-treat principle. Demographic and descriptive statistics will be calculated at baseline and at 9-months following the index overdose. The baseline characteristics and main outcomes between the intervention and control groups will be compared using the chi-square test and the two-sample t-test. 95% Confidence Intervals will be reported, and all hypothesis testing will be two-sided.

## Design Plan

- 3 Data is collected from study subjects that are not randomly assigned to a treatment. This includes surveys, "natural experiments," and regression discontinuity designs.

We will employ a quasi-experimental design to test the effectiveness of the MROT. Given the logistical and political considerations of evaluating the real-world implementation and effectiveness of a SAMHSA-funded program, a randomized controlled trial (RCT) is infeasible. Because this study is explicitly linked to, but not in total control over, the rollout of the SAMHSA-funded intervention, the study design must accommodate the fact that the SSA will implement a highly complex set of activities and is dependent on uptake of the program by each hospital ED. This logistical constraint makes it impossible to randomize en bloc. Therefore, a quasi-experimental design that rigorously controls for sources of confounding and bias is preferable. We anticipate there will be six hospital EDs in the implementation phase at the beginning of the study. Patients from these six hospitals who present with opioid overdose or a primary or secondary diagnosis of Opioid Use Disorder (OUD) and have contact with the MROT will be the intervention participants. Patients who present with these conditions at the hospitals that have not yet adopted the MROT program will serve as the control participants. We will analyze the data using a traditional approach that controls for sources of confounding and bias, while adjusting for clustering within hospitals. Also, we will analyze the data using a Propensity Score Matching approach to mitigate bias and support our ability to make causal inferences. All patient data will be obtained as de-identified secondary data from our state partners.

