#### 4.1 Sample Size:

In 2017, the six participating hospitals reported a total of 308 opioid-related poisoning visits to the ED, representing 37% (308/829) of the total visits statewide. Those numbers are highly conservative, because they are restricted to a small set of ICD-10 billing codes (primary diagnosis of T40.0, T40.1, T40.2, T40.3, T40.4, and T40.6). Other research found that using only ICD-9/10 billing codes related to opioid poisoning results in low sensitivity (as low as 25%). Additionally, rates of opioid-related visits have increased significantly over the past several years in Nevada (+12% 2010-2015, and +22% 2014-2015). Therefore, we anticipate that the actual number of intervention participants will be significantly higher. Using the findings from the sensitivity analysis above, we estimate the possible number of opioid-related poisonings for the 6 intervention hospitals to be 1232. The upper bound of the possible number of participants is represented by the total set of opioid-related ED encounters, which was 2635 in the six intervention hospitals in 2017, representing 37% (2635/7125) of encounters statewide. We anticipate 5% of control patients will access MAT compared to 33% of intervention patients. We anticipate that 7-12% of control patients will experience a non-fatal overdose in the 9 months following their index overdose, and that will be reduced by around 47% among intervention participants. According to unpublished data from the SSA, we anticipate 10% of control participants will die of an overdose in the next year compared to 5% in intervention participants.

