### Measured Variables

- 5 Intervention vs. Standard of Care: The exposure of interest is whether patients receive the MROT program or standard of care. Standard of care will be defined as receiving standard discharge instructions and a passive referral to local services. There are 2 primary outcomes

of interest that will be observed in the 9 months following the patient's initial contact with the MROT: MAT treatment initiation, and non-fatal overdose. Secondary outcomes of interest include MAT treatment retention and fatal overdose. All outcome variables will be measured using data that are available within the SSA databases and which will be provided to the research team in a linked, de-identified data set. Non-fatal overdose will be defined as experiencing an overdose that is treated by ED personnel in the six months subsequent to the initial contact with the MROT. In 2017 Nevada passed AB474, new opioid-related legislation that classified opioid overdose as a reportable condition. This law took effect July 1, 2017 and requires that ED clinicians make a name-based report to the public health authority when they treat an opioid overdose. This mandate should ensure that opioid overdoses are identified in the state surveillance databases. MAT treatment uptake will be measured in three ways. We will obtain records from the SSA that contain information about all patients enrolled in MAT through a state-funded or state-certified provider. First, to measure treatment uptake we will define a dichotomous variable representing whether patients enrolled in a MAT program. Second, we will define "time to treatment" as the time elapsed between the index overdose and enrollment in the MAT program. Third, we will follow MAT patients for 9 months and determine the duration of treatment participation for enrolled patients. Fatal overdose will be defined as a death of a patient that is determined to be opioid related (ICD-10 codes X42, X44, Y12, Y14, T40.0 – T40.6), as reported in the electronic death registry system. We will include all intentional, unintentional, and undetermined deaths in the initial analysis, and will conduct sub-analyses in which only unintentional and undetermined deaths are included.

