## Analysis Plan

- 6 We hypothesize that in the 9 months following their index overdose, patients exposed to the MROT will: H1: be more likely to initiate MAT (Primary outcome) H2: have fewer non-fatal ODs (Primary outcome) H3: be retained in MAT longer (Secondary outcome) H4: be less likely to die of a subsequent OD (Secondary outcome) All analyses will be conducted using the intent-to-treat principle. Demographic and descriptive statistics will be calculated at baseline and at 9-months following the index overdose. The baseline characteristics and main outcomes between the intervention and control groups will be compared using the chi-square test and the two-sample t-test. To test the hypotheses with the dichotomous outcome (initiation of MAT) and the ordinal outcome (incidence of non-fatal OD) we will use generalized linear mixed effects models (SAS PROC GLIMMIX) and Bayesian hierarchical models (SAS PROC MCMC) to account for the complexity of non-normal outcomes and intricate cluster effects due to the interdependence of patients within hospitals. The sensitivity analysis for Bayesian hierarchical models will also be performed. For the time to treatment, retention in treatment, and death due to subsequent OD outcomes, we will apply marginal Cox models (SAS PROC PHREG) to estimate the main effect of intervention exposure and use the robust sandwich covariance matrix estimation approach to account for the intracluster dependence. Individual demographic information including age, race, sex, drug of choice (heroin vs. prescription opioids), insurance type (e.g., Medicaid vs. private), and location of residence (urban vs. rural) will be included in the mixed effects models and marginal Cox models to control for potential confounding effects. We will obtain records from the SSA for 9 months prior to the index overdose for all participants, to allow us to control for prior history of non-fatal overdose and MAT utilization. Other covariates at the hospital level will include location (e.g., Northern Nevada vs. Southern Nevada, rural vs. urban) and hospital type (e.g., regional, university, trauma center, etc.). In addition to the statistical approach described above, we will also employ a propensity score (PS) matching approach as a secondary analysis. PS matching is particularly well-suited to "natural experiments" in which assignment to condition cannot be manipulated, such as the implementation of state programs. The approach involves calculating the probability of assignment to a treatment or exposure using logistic regression in which we enter observed characteristics that could influence assignment. In this case, known characteristics of patients such as age, sex, location of residence (rural vs. urban), previous history of overdose, or previous history of MAT enrollment. The PS reduces the large set of possible covariates that could influence selection into the intervention or control

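### The cohort admits patients with OUD but no overdose, while the hypotheses, time origin, overdose planning rate and sample size assume an index overdose, and index presentation type is in no listed model

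*Protocol*

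**What the plan says.** The Design Plan takes both arms from patients who "present with opioid overdose or a primary or secondary diagnosis of Opioid Use Disorder (OUD"). In the six participating hospitals there is a further condition: those who "have contact with the MROT will be the intervention participants". The overall goal in the Description matches this wide cohort, since it speaks of an "intervention for opioid overdose and/or opioid use disorder patients".

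Other parts of the Protocol describe a narrower group:

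- **Description, Aim 1:** subsequent overdose and "MAT uptake among patients presenting to a hospital ED for opioid overdose".
- **Hypotheses and Analysis Plan:** every hypothesis opens with "in the 9 months following their index overdose, patients exposed to the MROT will".
- **Measured Variables:** time to treatment is "the time elapsed between the index overdose and enrollment in the MAT program". The outcome window is otherwise counted from first contact with the MROT.
- **Analysis Plan:** the 9 months of earlier records are those before the index overdose, for every participant.
- **4.1 Sample Size:** 7-12% of controls are expected to "experience a non-fatal overdose in the 9 months following their index overdose".
- **4.2 Sample Size Rationale:** the samples of 829 and 3316 are counts of opioid poisonings.

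The patient covariates in the Analysis Plan are "age, race, sex, drug of choice (heroin vs. prescription opioids), insurance type (e.g., Medicaid vs. private), and location of residence (urban vs. rural"), plus earlier overdose and MAT history and hospital factors. The propensity score list gives age, sex, residence and the two history items. The interactions in 6.2 Exploratory Analysis name sex, drug of choice and rural or urban area. None of these lists includes whether the index visit was an overdose.

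**The concern.** Two things follow from the mismatch.

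First, some enrolled patients cannot be placed on the study clock. A patient with OUD alone has no index overdose. In the intervention arm that patient at least has an MROT contact, but in the control arm there is neither. Follow-up, time to treatment and the look-back that supplies the history covariates then have no defined start.

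Second, a patient seen for an overdose plausibly has a higher risk of another than a patient seen with an OUD diagnosis only. Earlier overdose history does not stand in for this, because it covers the months before the index visit. If the mix of presentation types differs between arms, no listed covariate removes the difference. The contact requirement, which applies to the intervention arm only, is a route by which the mix could come to differ. Non-fatal overdose, a primary outcome, is the most exposed.

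**Working it through.** **1. The Protocol's own sample figures.** Inputs from 4.1: 308 poisoning visits in the six hospitals, 829 statewide, code sensitivity as low as 25%.

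- 308 / 0.25 = 1232
- (829 - 308) / 0.25 = 521 / 0.25 = 2084
- 1232 + 2084 = 3316

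These match 4.2 exactly, so both planned samples count overdoses and not OUD diagnoses.

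**2. How much of the frame might be OUD-only.** 4.1 gives 7125 opioid-related ED encounters statewide as the basis of its upper bound.

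- Coded poisonings: 829 / 7125 = 11.6%
- After the 25% sensitivity scaling: 3316 / 7125 = 46.5%

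These are two estimates of one statewide share. The denominator counts encounters, not eligible patients.

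**3. Is the mix different by hospital group?**

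- Six hospitals: 308 / 2635 = 11.7%; scaled, 1232 / 2635 = 46.8%
- Elsewhere: 521 / (7125 - 2635) = 521 / 4490 = 11.6%; scaled, 2084 / 4490 = 46.4%

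Let c and t be the overdose shares in the control and intervention arms, and k the OUD-only risk divided by the overdose-patient risk (an assumption; the documents give no value). With no true effect,

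RR = [k + t(1 - k)] / [k + c(1 - k)].

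The shares above give RR of about 1.00-1.01 for k from 0 to 0.5. Hospital mix alone creates no bias.

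**4. Illustration of selection through contact.** Assume no effect, an overdose-patient risk of 9.5% (the middle of 7-12%), and shares of 11.6% in one arm and 46.5% in the other. That contrast between arms is illustrative, not observed.

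| k | Risk at 11.6% share | Risk at 46.5% share | RR, by direction |
|---|---|---|---|
| 0.25 | 9.5% x (0.116 + 0.884 x 0.25) = 3.20% | 9.5% x (0.465 + 0.535 x 0.25) = 5.69% | 0.56 or 1.78 |
| 0.5 | 9.5% x (0.116 + 0.884 x 0.5) = 5.30% | 9.5% x (0.465 + 0.535 x 0.5) = 6.96% | 0.76 or 1.31 |

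The planned reduction of about 47% is RR 0.53. A true 0.53 with the mix tilted against the intervention would appear as 0.53 x 1.31 = 0.69 to 0.53 x 1.78 = 0.94.

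**5. What the whole planned effect would need.** To mimic 0.53 with no effect, t = [0.53(k + c(1 - k)) - k] / (1 - k). To hide a true 0.53 completely, t = [(k + c(1 - k)) / 0.53 - k] / (1 - k).

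| k | Mimic, c = 46.4% | Hide, c = 11.6% | Hide, c = 46.4% |
|---|---|---|---|
| 0 | t = 24.6% | t = 21.9% | t = 87.5% |
| 0.1 | t = 19.4% | t = 31.7% | t = 97.4% |
| 0.25 | t = 8.9% | t = 51.4% | impossible |
| 0.5 | impossible | impossible | impossible |

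At k = 0.1, moving from 11.6% to 31.7% means contact odds about (0.317/0.683) / (0.116/0.884) = 3.5 times higher for overdose patients. Moving from 46.4% to 97.4% would need about 43 times.

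**6. MAT initiation.** Suppose uptake is 5% in overdose patients and 33% in OUD-only patients, with no effect. Overdose shares of 90% (control) and 30% (intervention) give 0.9 x 5% + 0.1 x 33% = 7.8% and 0.3 x 5% + 0.7 x 33% = 24.6%. Only complete separation of the two types reaches 5% against 33%.

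**7. Planning rate in a pooled cohort with balanced arms.** Control risk = (7-12%) x [s + (1 - s)k], where s is the overdose share. For k = 0.25-0.5 it is 2.4-6.7% at s = 11.7% and 4.2-8.8% at s = 46.8%, in place of 7-12%.

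**The case against.** The wide cohort is plainly intended. The overall goal names OUD patients, the upper bound in 4.1 counts all opioid-related encounters, and the planned MAT rates (5% against 33%) and death rates (10% against 5%) are not tied explicitly to an index overdose. The covariate lists are worded as inclusions or examples, so an unseen SAP could add index type. Nothing in the documents shows that contact depends on presentation type, and the risk ratios above are crude, before adjustment for overdose and MAT history, drug of choice and hospital. Index type would itself be recorded with error: 4.1 says billing codes may miss up to three quarters of poisonings, and Measured Variables says only that mandatory reporting should capture them.

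Most of this stands, and it limits the point. It does not remove the conflict between the eligible cohort and the population in Aim 1, the hypotheses, the look-back and the overdose planning rate. Nor is a missing time origin for OUD-only controls a detail left for later, because the Protocol fixes the origin in terms that this group cannot meet.

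A reader might infer that case mix can mimic or hide the whole planned effect. The documents do not support that as a general statement. The shares by hospital group are nearly equal, the illustrative ratios stop short of 0.53 and, for masking, short of 1.0, and the full effect is reached only under lower assumed risk ratios or more extreme shares. A reader might also take it that half to nine tenths of patients will have no index overdose. That range comes from encounter counts and an uncertain code sensitivity, and is not an estimate of the enrolled cohort.

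**Conclusion.** The point holds as an inconsistency of population and time origin, joined to an omitted covariate. On the text alone, OUD-only controls have no defined start of follow-up or look-back, and the 7-12% rate and the samples of 829 and 3316 describe overdose patients only.

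The bias is possible but not shown. It needs contact with the MROT to depend on presentation type, and its size depends on an OUD-only risk and an arm-specific mix that the documents do not give. Under the stated illustration the null risk ratio for non-fatal overdose is 0.56-0.76 or 1.31-1.78, a material distortion beside a planned 0.53. For MAT initiation, mimicking the whole planned gap is implausible.

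It might also seem to follow that overdose patients must become the primary set for the overdose hypotheses. The documents do not settle that, because the overall goal includes OUD patients. It is a choice of estimand for the sponsor to state.

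**What to change.** - Reconcile the target population across the Description, Hypotheses, Design Plan, 4.1, Measured Variables and the Analysis Plan.
- Use the index ED visit as the single time origin and look-back anchor for all patients in both arms.
- Add index presentation (overdose, or OUD without overdose) to all mixed, Bayesian and Cox models and to the propensity score. Derive it from index-visit codes and the mandatory overdose reports, and acknowledge coding error.
- Report the non-fatal and fatal overdose outcomes by index type, and add index type to the interactions in 6.2.
- State that the 7-12% rate and the samples of 829 and 3316 refer to overdose patients.

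The cost is wording and one covariate derived from data already needed for eligibility, with some misclassification. Planning figures for the pooled cohort will look less favourable, because its expected control risk for non-fatal overdose is lower than 7-12% if OUD-only patients are at lower risk.

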#### 4.2 Sample Size Rationale:

The alpha significance level of the power analysis is set to 0.05. At least 82% power will be achieved to detect a small effect size of 0.2 under the anticipated conservative sample size. Under different assumptions of effect size, such as medium effect size of 0.5 and large effect size of 0.8, our analysis strategy will have at least 99% power. For reasonably anticipated sample size 3316 (1232 intervention and 2084 control), at least 99% power will be achieved to detect as small as 0.1 effect size. Therefore, a very conservative sample of 829 (308 intervention and 521 control) patients will be sufficient to evaluate the primary outcomes. R package pwr was used for power analysis. To be our best knowledge, very few existing power analysis approaches can be applied to hierarchical models. In addition to the primary aims of the proposal, data will be used to develop a statistically reliable and computationally efficient power analysis procedure for hierarchical models and implement the proposed approach in an R package and a SAS macro.

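### Intervention patients are defined by actual MROT contact and controls are not filtered, so the comparison is as-treated although the protocol calls it intent-to-treat and counts every visit at the six hospitals in its sample size

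*Protocol*

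**What the plan says.** Five parts of the protocol bear on who is compared with whom.

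- **Design Plan, allocation.** The study is not randomised: "Data is collected from study subjects that are not randomly assigned to a treatment".
- **Design Plan, groups.** Patients at the six hospitals with an opioid overdose or an OUD diagnosis "and have contact with the MROT will be the intervention participants". For controls: "Patients who present with these conditions at the hospitals that have not yet adopted the MROT program will serve as the control participants". The control definition has no contact or acceptance condition.
- **Measured Variables.** "The exposure of interest is whether patients receive the MROT program or standard of care". The primary outcomes are those "of interest that will be observed in the 9 months following the patient's initial contact with the MROT".
- **Hypotheses and Analysis Plan.** "All analyses will be conducted using the intent-to-treat principle". Both sections also place the outcomes in the 9 months after the index overdose, not after MROT contact.
- **Sample Size (4.1) and Sample Size Rationale (4.2).** "In 2017, the six participating hospitals reported a total of 308 opioid-related poisoning visits to the ED". Section 4.2 takes that 308 as the intervention group: "a very conservative sample of 829 (308 intervention and 521 control) patients will be sufficient to evaluate the primary outcomes".

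**The concern.** Intent-to-treat needs groups fixed by something that happens before treatment and does not depend on receiving it. In a non-randomised programme evaluation the natural candidate is the hospital, with or without MROT, at which the patient presents. The Design Plan instead makes receipt of contact a condition of membership in one group only.

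Two things follow. First, eligible patients at MROT hospitals who are not contacted drop out of the analysis, while their counterparts at control hospitals stay in. Any difference in prognosis between contacted and uncontacted patients then becomes part of the estimated effect. Second, follow-up under Measured Variables starts at an event that control patients never have, so the two groups have no common time zero.

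Both primary outcomes and the fatal-overdose hypothesis rest on this comparison. Followed as written, the plan would produce an as-treated estimate and report it as intent-to-treat. A later analysis plan cannot settle this quietly, because the protocol itself fixes the group definitions.

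**Working it through.** **1. The definitions side by side**

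| Place | Intervention group implied |
|---|---|
| Design Plan | eligible presenters at the six hospitals with MROT contact |
| Measured Variables | patients who receive the programme, followed from contact |
| Hypotheses, Analysis Plan | grouping independent of receipt (intent-to-treat), followed from the index overdose |
| Sample Size, Sample Size Rationale | all opioid-poisoning visits at the six hospitals |

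The first two rows agree with each other and conflict with the last two.

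**2. The sample size contains no contact fraction**

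The protocol's counts reproduce from visits alone:

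- 308/829 = 37%, and 829 − 308 = 521.
- At 25% sensitivity of billing codes, 308/0.25 = 1232 and 829/0.25 = 3316, and 3316 − 1232 = 2084.

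Nothing is multiplied by the share of patients reached. If a fraction c is reached, the Design Plan's intervention group has 308c patients: 231, 154 or 77 at c = 0.75, 0.5 or 0.25.

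For scale, a standardised difference of 0.2 at two-sided 0.05 has 79.5% power with 308 v 521 and 59% with 154 v 521. (The protocol's 82% matches an equal split of 829. That is a separate matter, and this point does not depend on it.)

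**3. What contact selection could do with no true effect**

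The protocol gives neither the contacted fraction f nor the risk r of uncontacted relative to contacted patients. Both are assumed here. Suppose all presenters at MROT hospitals have the same average risk as controls. If contacted patients have risk p, all presenters have p[f + (1 − f)r], so

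apparent RR = 1/[f + (1 − f)r].

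| f | r | Calculation | Apparent RR |
|---|---|---|---|
| 0.8 | 1.2 | 1/(0.8 + 0.24) | 0.96 |
| 0.6 | 1.5 | 1/(0.6 + 0.6) | 0.83 |
| 0.4 | 2 | 1/(0.4 + 1.2) | 0.63 |
| 0.6 | 1/1.5 | 1/(0.6 + 0.267) | 1.15 |
| 0.4 | 0.5 | 1/(0.4 + 0.3) | 1.43 |

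The planned 47% reduction in non-fatal overdose is an RR of 0.53. These values are unadjusted. The listed covariates (demographics, drug of choice, insurance, residence, nine-month history, hospital factors) and the propensity score include no measure of being reached or willing to engage.

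**4. What a hospital-based comparison costs in power**

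Inputs from Sample Size: MAT 5% v 33%; non-fatal overdose 7–12% in controls, with a 47% reduction. Assume that uncontacted patients at MROT hospitals have the control rate, that contacted patients get the full planned effect, and that patients are independent. The expected rates at MROT hospitals are then

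- MAT: 0.05 + 0.28c
- overdose: p0(1 − 0.47c), where p0 is the control rate.

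At c = 0.4 these are 16.2% for MAT, and 5.7% (p0 = 7%) or 9.7% (p0 = 12%) for overdose. Power from the two-sided two-proportion normal approximation at 0.05, with overdose shown for p0 = 7% and 12%:

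| c | MAT, 308/521 | Overdose, 308/521 | Overdose, 1232/2084 |
|---|---|---|---|
| 1 | >99% | 50%, 76% | 98%, >99% |
| 0.75 | >99% | 29%, 49% | 83%, 98% |
| 0.5 | >99% | 15%, 23% | 46%, 72% |
| 0.4 | >99% | 11%, 16% | 31%, 51% |
| 0.25 | 94% | 6%, 9% | 15%, 23% |

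For comparison, the contact-only contrast at c = 0.4 has 23% or 43% power for overdose with 308c v 521, and 81% or 98% with 1232c v 2084. Those figures assume that the contrast is unbiased, which is the point in doubt.

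**The case against.** The best defence is that the hypotheses concern patients exposed to the MROT, so a contact-based comparison answers the question asked. On that view intent-to-treat only means keeping every contacted patient whatever their later engagement. This is a possible reading, and a hospital-based comparison does change the question. But it leaves a filtered group against an unfiltered one, and it does not explain an intervention N made of all visits.

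The second defence is that the plan adjusts for prior overdose and prior MAT use, which may partly stand in for engagement, and adds propensity matching. That may reduce the bias. Neither method reaches unmeasured reasons for contact, and matching is a secondary analysis.

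The third is the loss of overdose power shown above. It is real and must be disclosed.

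A reader might also infer more than the documents support:

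- **That contacted patients are self-selected.** The protocol does not say whether contact depends on patient acceptance, staff referral or team availability. Selected by contact is as far as it goes.
- **That the bias must favour MROT.** If teams are called to the more severe cases, the same formula gives an RR above 1.
- **That surviving long enough to be contacted builds in a mortality advantage.** The fatal-overdose hypothesis concerns a subsequent overdose, so under that wording deaths at the index visit are not events in either group.
- **That exposure is confounded with calendar time.** Six EDs are expected to be implementing at the start, so the groups can run concurrently. The control wording allows for later adoption, but this does not establish confounding.

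**Conclusion.** The point holds as an internal contradiction with consequences for the primary analyses. The group and exposure definitions describe an as-treated comparison. The intent-to-treat statement and the sample size describe a hospital-based one. All four cannot stand together unless every eligible patient at the six hospitals is contacted, which the protocol does not claim.

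How far the estimates would be off, and in which direction, cannot be said from the documents. The range of 0.63 to 1.43 with no true effect rests on assumed contact fractions of 40–60%, assumed risk ratios of 0.5 to 2 and no adjustment. It shows that the selection could matter, not that it will. The power figures rest on independent patients and would be lower with clustering by hospital. They also rest on the planned effect applying in full to contacted patients and not at all to others.

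**What to change.** Make the intent-to-treat comparison all eligible patients who present at an MROT hospital while the programme is live, contacted or not, against all eligible patients at hospitals without MROT. Start follow-up at the index ED visit in both groups, and align Measured Variables with this. Report the contact-based comparison separately, labelled as-treated.

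If the contact definition is kept as primary, the minimum is to remove the intent-to-treat wording from Hypotheses and Analysis Plan and to restate the intervention N as the expected number of contacted patients.

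In either case, restate power for both primary outcomes over a range of contact fractions.

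The cost in data should be small. The statewide hospital, mortality and MAT files described in the Sampling Plan should already hold uncontacted patients; the dates on which each hospital's programme was live are also needed. The cost in power falls on non-fatal overdose. With 308/521 it is about 11–16% at 40% contact and 15–23% at 50%; with 1232/2084 it is 31–51% and 46–72%. MAT initiation keeps over 99% at 40% contact even with 308/521. The sponsor should see these figures before choosing.
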